#### Criteria for withdrawing a patient from the study

2.8.3

Patients must be withdrawn from the study in any of the following situations: 1) any adverse event for which clinicians consider it necessary to withdraw trial experimental therapy; 2) the patient requests to be withdrawn from the study (at any time during the patient's participation); 3) the principal investigator (PI) considers that there has been a serious protocol violation; 4) lost to follow-up; and 5) pregnancy during the study.

When a patient withdraws from the study, the investigator records the reason/s in the clinical chart and the electronic case report form (eCRF). If the reason for withdrawal is a serious adverse event, the patient must be followed-up until resolution or stabilisation of the event. Patients who withdraw will not be replaced.

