### Randomization

2.4

On day 0, patients are centrally and randomly assigned using the RedCap computer platform that allows data collection and patient randomization. Patients are not stratified by baseline variables. Participants are randomized in a 1:1 ratio into one of two study groups: methylprednisolone pulses, tacrolimus and SoC, or SoC alone.

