### Study visits

2.6

All patients are followed from day 0 through day +56 or death. The planned visits are: 1) randomization visit (day 0) in which the patient is screened and eventually included in the study; 2) Hospitalization visits that are variable according to the period of admission; 3) Visits on day +28 ± 3 and on day +56 ± 3 from randomization. These visits are face-to-face to evaluate whether patients present a relapse or worsening of the disease, as well as the presence of adverse events or mortality. Specific procedures that are performed on each visit are detailed in Table 1 and the *evaluation methods* section.

**Table 1 tbl1:** Flow-chart of the trial showing the procedures that will be conducted in each visit.

	Randomization visit (day 0)	Hospitalization visits (days n)	Visit 28 ± 3 days after the start of treatment	Visit 56 ± 3 days after the start of treatment
Inclusion/exclusion	x			
Informed consent	x			
Randomization	x			
Demographics Comorbidities	x			
COVID-19 clinical data	x			
Vital signs	x	x	x	x
8-point Ordinal scale	x	x	x	x
Analysis (Hematology, Chemistry, Coagulation)	x	x	x	x
Tacrolimus levels		x		
Cytokines	x	x	x	x
Viral load (blood)	x	x	x	x
Nasopharyngeal SARS-CoV-2 PCR	x		x	x
Clinical stability	x	x	x	x
Lung tests (x-ray, CT scan, chest US, 6MWT, functional tests)	x	x (1)	x (1)	x
Study treatment	x	x	x	x
Concomitant medication	x	x	x	x
AE registration	x	x	x	x

(1) according to the attending physician.

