#### Statistical considerations

2.9.2

A descriptive analysis of the study variables will be carried out. Continuous variables will be described as mean and Standard Deviation (SD) or as median and range; and categorical variables as absolute frequencies and percentages. The main analysis will be performed when all patients reach clinical stability or failure. If patients are in hospital for 56 days, they will be considered clinical failures. Comparison between average time to achieve clinical stability between the two study groups will be measured using the log-rank test. To quantify the degree of association, hazard ratio will be estimated with a Cox proportional hazards model using a 95% confidence interval.

Efficacy analyses will be performed for the intention to-treat (ITT) population. If a proportion of subjects >10% is detected to have relevant deviations from the protocol (for example, non-compliance with the selection criteria, non-compliance or inability to receive the trial treatment), the per protocol (PP) analysis will exclude those subjects with such deviations. If this group is defined, all exploratory efficacy analyses will be repeated as a sensitivity test.

As additional analysis, a Cox proportional hazards model, adjusted for clinically relevant confounding factors such as age, sex, comorbidities using the Charlson index, indexes to assess the severity of pneumonia (PSI and CURB-65), index of organic dysfunction (SOFA) and inflammatory parameters will be performed. In addition, prespecified subgroup analyses involving sensitivity analysis will be used to evaluate outcomes in patients not receiving invasive mechanical ventilation.

For evaluation of secondary variables, we will calculate unadjusted and adjusted estimations of effect size and the corresponding 95% confidence intervals using linear, logistic or proportional hazards Cox regression. Study adverse events will be described according to their severity and relationship with other treatments, and will be compared between treatment groups. Midway through recruitment, i.e. 21 patients per arm, an intermediate efficacy and safety analysis will be performed. For this, a correction of the type I error will be applied following Lan-DeMets (O'Brien – Fleming) in evaluation of efficacy.

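### Section 2.8.3 ends study participation, not only treatment, when experimental drug is stopped for an adverse event; outcomes to day 56 could then be missing, more often in the experimental arm

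*Protocol article*

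**What the plan says.** Section 2.8.3 of the protocol article opens with a mandatory rule: "Patients must be withdrawn from the study in any of the following situations". Three of its five situations matter here:

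- criterion 1, "any adverse event for which clinicians consider it necessary to withdraw trial experimental therapy";
- criterion 3, "the principal investigator (PI) considers that there has been a serious protocol violation";
- criterion 5, pregnancy.

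The other two are the patient's own request and loss to follow-up. The section states one follow-up duty after withdrawal: "If the reason for withdrawal is a serious adverse event, the patient must be followed-up until resolution or stabilisation of the event". It adds: "Patients who withdraw will not be replaced".

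Elsewhere the article says:

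- Section 2.6, Study visits: "All patients are followed from day 0 through day +56 or death".
- Section 2.9.2, Statistical considerations: "Efficacy analyses will be performed for the intention to-treat (ITT) population". Patients with relevant deviations are left out only of a per-protocol analysis, which is run if they exceed 10%.
- Section 2.4, Randomization: the two groups are "methylprednisolone pulses, tacrolimus and SoC, or SoC alone".
- Section 2.5, Treatment: a serious medication-related adverse event is a reason to discontinue experimental treatment. Leaving the study is not mentioned.
- Section 2.8.1, Primary end point: death, or a grade 3 or 4 adverse event attributed to trial treatment, is treatment failure.
- Section 2.8.2, Secondary endpoints: these include mortality at days 28 and 56 and the ordinal scale to day 56.

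**The concern.** Stopping a drug and leaving a trial are different events, and section 2.8.3 makes the first trigger the second. Controls receive no experimental therapy, so criterion 1 can remove patients from one arm only. An ITT label keeps such patients in the analysis set but does not supply outcomes that nobody recorded after they left.

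Time to clinical stability, the ordinal scale and vital status at days 28 and 56 are all at stake. If the patients removed differ in prognosis from those who stay, the randomised comparison is distorted. Missing vital status also weakens the safety comparison, which matters for an immunosuppressive combination tested in 42 patients per arm.

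**Working it through.** **1. Sections side by side.**

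- An adverse event stops the drug: 2.5 ends treatment (for serious drug-related events); 2.8.3 ends study participation (for any adverse event, with no grade or attribution required).
- Follow-up: 2.6 runs to day 56 or death for everyone. The only post-withdrawal follow-up that 2.8.3 states concerns serious adverse events and runs to resolution or stabilisation.
- Violators: 2.9.2 keeps them in the ITT analysis; 2.8.3 takes them out of the study.
- Primary outcome after withdrawal: 2.8.1 defines it for deaths and for attributed grade 3–4 events. For lower-grade or non-attributed events, violations and pregnancy, the article does not say whether a withdrawn patient is censored or counted as a failure.

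Criterion 1 is confined to the experimental arm by construction. Criteria 3 and 5 are open to both arms; criterion 3 is a judgement made after randomisation in an open-label trial.

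**2. The plan's own allowance.** Inputs from 2.9.1: hazard ratio 0.52, power 80%, type I error 0.05 (taken as two-sided), 5% withdrawal. Freedman's formula gives (1.960 + 0.842)² × (1.52/0.48)² = 78.7, so 79 events. Then 79/0.95 = 83.2, rounded up to 84, or 42 per arm. The stated figure is reproduced. The allowance is 0.05 × 42 = 2.1 patients per arm.

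**3. Power.** With extra experimental-arm withdrawal w, the available events are 42 × 0.95 + 42 × (0.95 − w), and power is Φ(√events × 0.48/1.52 − 1.960). The values of w are assumed.

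| w | events | power |
|---|---|---|
| 0 | 79.8 | 80.5% |
| 5% | 77.7 | 79% |
| 10% | 75.6 | 78% |
| 20% | 71.4 | 76% |
| 30% | 67.2 | 74% |

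The loss of power is modest.

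**4. Bias under no true effect.** Assumed model: 35% of patients recover slowly, with a hazard 0.1 to 0.75 times that of the rest; pooled median 16 days (the plan's control figure); 56-day limit; withdrawals only among slow patients in the experimental arm, on days 1–7; 200,000 per arm. Hazard ratios are experimental versus control, so above 1 favours the experimental arm. The design effect on this scale is 1/0.52 = 1.92.

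| Withdrawn from experimental arm | All censored | All counted as failures | Half each |
|---|---|---|---|
| 5% | 1.01–1.06 | 0.91–0.97 | 0.96–1.01 |
| 10% | 1.01–1.12 | 0.83–0.95 | 0.91–1.02 |
| 15% | 1.03–1.18 | 0.77–0.91 | 0.88–1.02 |
| 20% | 1.04–1.28 | 0.70–0.88 | 0.83–1.04 |

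A separate run with 21% withdrawn gave 1.30 at a slow-class hazard of 0.1 and 1.11 at 0.5. When withdrawal is unrelated to prognosis and patients are censored, the ratio is about 1.00.

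**5. Type I error at the trial's size.** A second assumed model has 42 per arm, and every withdrawal-prone patient in the experimental arm who is not yet stable is censored between days 1 and 10 (6,000 runs). With full follow-up the two-sided error is about 5%. With censoring, and a recovery hazard in prone patients of 0.5 to 0.25, it is 6–8% with 10% prone, 8–16% with 20% and 11–24% with 30%, nearly all favouring the experimental arm. It stays at about 5% if prone patients recover like the others. This model is harsher because it can empty one arm of its slow patients: with 20% prone the mean hazard ratio is 1.14 to 1.28 over that range, and 1.41 at a recovery hazard of 0.1.

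**6. Mortality.** If k of 42 patients in an arm have unknown vital status, that arm's mortality is known only to within k/42: 4.8 percentage points for k = 2, 9.5 for k = 4, 19.0 for k = 8.

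**The case against.** The strongest objection concerns direction. It is tempting to infer that the rule must favour the experimental arm. The article does not support that. No section says withdrawn patients are censored, and 2.8.1 already counts attributed grade 3–4 events and deaths as failures. Many events serious enough to stop the drug may fall there, and the table shows that the ratio then moves the other way. This stands.

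Four further readings also go too far:

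- That ITT is abandoned. Section 2.9.2 retains it; the exposure is missing data within the ITT set.
- That the sickest experimental patients are lost as a class. Ventilation, ECMO and severe infection appear in 2.5 as reasons to stop treatment, and progression to ventilation or ECMO is not in itself a 2.8.3 criterion.
- That follow-up after a serious event is capped. Section 2.8.3 states a duty, not a maximum, and 2.11.2 asks for further information until the end of the study or a definitive outcome.
- That criterion 3 works against one arm. It applies to both, and any asymmetry is conjecture.

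A full protocol or analysis plan, not shown, may also cover data collection after withdrawal. That does not remove the point, which rests on a mandatory rule stated here that conflicts with other stated text. A failure label likewise supplies no later vital status or ordinal-scale value, and it does not reach lower-grade events, violations or pregnancy.

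**Conclusion.** The contradiction is certain on the face of the text. Section 2.8.3 ends study participation in situations where 2.6, 2.8.2 and 2.9.2 need outcomes to continue and where 2.5 stops treatment only. One trigger can occur only in the experimental arm, so missing outcomes could be more frequent there.

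The size is conditional, because the article gives neither a withdrawal rate nor a censoring rule. If withdrawn patients are censored and have poor prognosis, the null hazard ratio shifts towards the experimental arm, by about 1.01–1.06 at 5% and 1.04–1.30 at about 20%; the harsher model goes beyond this only at its most extreme assumption. If withdrawal is unrelated to prognosis, the shift is about nil. If withdrawn patients count as failures, it is 0.91–0.97 at 5% and 0.70–0.88 at 20%, against the experimental arm. The stated sample size is not in error. The matter deserves correction during the trial because follow-up that was not collected may not be recoverable at analysis.

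**What to change.** Reconcile sections 2.5, 2.6, 2.8.1, 2.8.3 and 2.9.2 by separating discontinuation of study drug from withdrawal from the study.

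- Criteria 1, 3 and 5 should not end follow-up. Every randomised patient is followed for stability, safety and vital status to day 56 and analysed in the allocated arm.
- Data collection ends only when consent is withdrawn or the patient is truly lost to follow-up.
- Sections 2.8.1 and 2.9.2 should agree on how a patient who stops the drug enters the primary analysis: as a failure where 2.8.1 says so, otherwise with the observed time to stability.

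The rules on when drug is stopped are not changed. The cost is an amendment of wording. The day-28 and day-56 visits are already planned for all patients, and the sample size stays at 84.

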### Statistical analysis

2.9

#### Determination of sample size

2.9.1

The median time to clinical stability in the control group is expected to be 16 days. If the hazard ratio of clinical stability of control patients in relation to the patients in the experimental group were 0.52, it would be necessary to include 42 patients in each group in order to be able to reject the null equality hypothesis with a power of 80%. The probability of Type I error associated with this hypothesis test is 0.05 and includes 5% of withdrawal.

#### Statistical considerations

2.9.2

A descriptive analysis of the study variables will be carried out. Continuous variables will be described as mean and Standard Deviation (SD) or as median and range; and categorical variables as absolute frequencies and percentages. The main analysis will be performed when all patients reach clinical stability or failure. If patients are in hospital for 56 days, they will be considered clinical failures. Comparison between average time to achieve clinical stability between the two study groups will be measured using the log-rank test. To quantify the degree of association, hazard ratio will be estimated with a Cox proportional hazards model using a 95% confidence interval.

Efficacy analyses will be performed for the intention to-treat (ITT) population. If a proportion of subjects >10% is detected to have relevant deviations from the protocol (for example, non-compliance with the selection criteria, non-compliance or inability to receive the trial treatment), the per protocol (PP) analysis will exclude those subjects with such deviations. If this group is defined, all exploratory efficacy analyses will be repeated as a sensitivity test.

As additional analysis, a Cox proportional hazards model, adjusted for clinically relevant confounding factors such as age, sex, comorbidities using the Charlson index, indexes to assess the severity of pneumonia (PSI and CURB-65), index of organic dysfunction (SOFA) and inflammatory parameters will be performed. In addition, prespecified subgroup analyses involving sensitivity analysis will be used to evaluate outcomes in patients not receiving invasive mechanical ventilation.

For evaluation of secondary variables, we will calculate unadjusted and adjusted estimations of effect size and the corresponding 95% confidence intervals using linear, logistic or proportional hazards Cox regression. Study adverse events will be described according to their severity and relationship with other treatments, and will be compared between treatment groups. Midway through recruitment, i.e. 21 patients per arm, an intermediate efficacy and safety analysis will be performed. For this, a correction of the type I error will be applied following Lan-DeMets (O'Brien – Fleming) in evaluation of efficacy.

The IDIBELL Biostatistical Unit will perform analysis and analysts will be blind to the treatment received by the patients (intervention vs. usual care). R version 3.6.2 or higher for Windows (R Foundation for Statistical Computing, http://www.r-project.org) will be used for data treatment and analysis.

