### Treatment

2.5

Patients are being randomly assigned to one of the following arms:1. Experimental: methylprednisolone pulses of 120 mg/day are administered on 3 consecutive days (if not previously administered) and immediate release tacrolimus is administered twice daily until clinical stability is achieved. Tacrolimus dosing is individualized through therapeutic drug monitoring (TDM) to achieve blood trough levels of 8–10 ng/mL. In addition, patients in the experimental arm can receive standard of care (SoC) for their management in accordance with treating physicians.2. Control (SoC): SoC includes measures of supplemental oxygen and respiratory support, fluid therapy, antipyretic treatment, postural measures, low molecular weight heparins, and may also include other treatments, whether antiviral or immunosuppressive drugs, or those necessary at the discretion of the treating physician, except for cyclosporine and/or tacrolimus.

The experimental drugs start immediately after having been randomly assigned to this group. The experimental treatment is discontinued after “*clinical stability*”, which is achieved after fulfilling all of the following criteria for 48 consecutive hours: body temperature ≤37.5 °C; PaO2/FiO2 > 400 and/or SatO2/FiO2 > 300; and respiratory rate ≤24 rpm.

Experimental treatment is also discontinued if the included patient has a severe or potentially severe infection, required invasive mechanical ventilation, extracorporeal membrane oxygenation (ECMO), or has any serious medication-related adverse event (of special interest refractory HTA, decrease of more than 50% of the GFR compared to the baseline, or ventricular tachycardia).

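### The main hazard ratio is unadjusted in an unstratified 84-patient trial, and the supportive adjusted model does not name the baseline oxygenation ratio while listing three overlapping severity scores

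*Protocol article*

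**What the plan says.** Section 2.9.2 (Statistical considerations) compares time to clinical stability by a log-rank test and quantifies the effect by a Cox hazard ratio for which no covariate is named. As an additional analysis it gives a "Cox proportional hazards model, adjusted for clinically relevant confounding factors such as age, sex, comorbidities using the Charlson index", and the list continues with PSI, CURB-65, SOFA and inflammatory parameters whose number is not stated.

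Section 2.4 (Randomization) says: "Patients are not stratified by baseline variables".

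Section 2.9.1 (Determination of sample size) expects a control median of 16 days and a "hazard ratio of clinical stability of control patients in relation to the patients in the experimental group were 0.52". On that basis "it would be necessary to include 42 patients in each group" for 80% power. It adds: "The probability of Type I error associated with this hypothesis test is 0.05 and includes 5% of withdrawal".

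Oxygenation appears in three other places. Section 2.2.1 requires PaO2/FiO2 below 300 or SatO2/FiO2 below 220 at entry, with no lower limit. Section 2.5 makes a ratio above 400 (PaO2) and/or above 300 (SatO2) one of three components of clinical stability, with temperature and respiratory rate. Section 2.7.1 records one or both ratios on day 0 and says that PSI, CURB-65 and SOFA are computed from the day-0 data.

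Section 2.5 also gives "methylprednisolone pulses of 120 mg/day are administered on 3 consecutive days (if not previously administered", so corticosteroid exposure before randomization will differ between patients.

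**The concern.** A patient who enters on a given ratio must climb from below the entry limit to above the stability limit on that ratio to have the event. The day-0 value is the starting distance. Temperature and respiratory rate have no entry limit, so some patients may already satisfy those two components at randomization. Baseline oxygenation is therefore a natural candidate for a strong predictor of time to stability, yet neither the main nor the additional model names it.

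When a strong predictor is left out of a Cox model, the treatment hazard ratio moves towards 1 and power falls. The trial has little reserve against this, and without stratification nothing in the design balances the predictor. The additional model is poorly suited to make up the loss: it spends its parameters on three scores built from the same day-0 data, alongside age, which is also entered separately, and its list is open.

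**Working it through.** **Inputs.** From section 2.9.1: hazard ratio 0.52 (control versus experimental), control median 16 days, power 80%, alpha 0.05, withdrawal 5%, 42 per arm. From section 2.8.1: follow-up for the endpoint to day 56. Assumed: two-sided alpha (sidedness is not stated), exponential times, and the log hazard ratio g per SD of baseline oxygenation, for which the protocol gives no figure.

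**1. The plan's own figure.** Freedman: events = (1.96 + 0.842)² × [(1 + 0.52)/(1 − 0.52)]² = 7.85 × 10.03 = 78.7, so 79. With withdrawal: 79/0.95 = 83.2, so 84, or 42 per arm. The stated size reproduces for an unadjusted comparison.

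**2. Reserve.** Probability of the event by day 56: control 1 − 2^(−56/16) = 0.912; experimental 1 − 2^(−56/(16 × 0.52)) = 0.991; mean 0.951. Expected events: 84 × 0.95 × 0.951 = 75.9. Schoenfeld power: Φ(√(75.9/4) × |ln 0.52| − 1.96) = Φ(0.89) = 81%.

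**3. Chance imbalance.** SD of a difference in baseline means: √(2/42) = 0.218 SD. P(|difference| > 0.3 SD) = 2[1 − Φ(0.3/0.218)] = 17% for any one covariate.

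**4. Power with and without adjustment.** Cox simulations with day-56 censoring, 5% withdrawal (80 evaluable of 84 in the re-derivation) and 1,500 replicates. Where a range is shown, the simulation was repeated independently. Hazard ratios are control versus experimental.

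*Reading A: 0.52 is the covariate-conditional hazard ratio.*

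| g per SD | Unadjusted HR | Unadjusted power | Adjusted power |
|---|---|---|---|
| 0 | 0.52 | 80% | 80% |
| 0.3 | 0.53–0.54 | 75–76% | 80–81% |
| 0.4 | 0.55 | 72% | 81% |
| 0.5 | 0.56–0.57 | 68–69% | 80–81% |
| 0.7 | 0.60–0.61 | 56–60% | 78–83% |
| 1.0 | 0.64 | 44% | 76% |

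*Reading B: the unadjusted hazard ratio is itself about 0.52.*

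| g per SD | Unadjusted HR | Unadjusted power | Adjusted power |
|---|---|---|---|
| 0.4 | 0.53 | 74% | 83% |
| 0.7 | 0.52 | 77% | 93% |
| 1.0 | 0.52 | 76% | 97% |

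Under the null, the unadjusted test rejected in 3.9–5.3% of replicates and the one-covariate model in 4.3–6.1%. The Monte Carlo standard error is √(0.05 × 0.95/1500) = 0.6 points.

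**5. Where the gain comes from.** At g = 0.7 under reading A, the mean log hazard ratio is ln(1/0.597) = 0.516 unadjusted and ln(1/0.513) = 0.667 adjusted. Dividing by the z implied by each power (1.96 + 0.16 and 1.96 + 0.76) gives standard errors of about 0.24 and 0.25. The standard error hardly changes; adjustment recovers the effect that omission shrinks. Precision therefore improves relative to the effect, not in absolute terms.

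**6. The listed model.** Treatment, age, sex, Charlson, PSI, CURB-65, SOFA and one inflammatory marker make 8 parameters; five markers make 12. At 76 events that is 76/8 = 9.5 down to 76/12 = 6.3 events per parameter. A stand-in model with three scores, each correlated 0.5 with oxygenation (assumed), plus seven covariates of no prognostic value gave power of 76–85% under reading B, where adjusting for oxygenation itself gave 83–97%. Its type I error was 7.5–8.8%. Adjusting for a single score correlated 0.5 with oxygenation recovered little under reading A: 72% to 74% at g = 0.4, and 57% to 61% at g = 0.7.

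**The case against.** An unadjusted log-rank test in a randomized trial is valid. The stated sample size was built for it, and its simulated type I error is correct. Chance imbalance is ordinary sampling error that the test and confidence interval already allow for. The smaller unadjusted hazard ratio is a marginal quantity, different from the conditional one, and not a biased estimate. All of this stands. A reader might infer that the primary analysis is biased or the trial mis-sized; the protocol does not support either.

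The covariate list is introduced as examples, and an analysis plan that is not shown could close it. That also stands, and it limits the point to what the article names. It does not change the article's choice of an unadjusted main estimate with adjustment as an addition.

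The scores are computed from day-0 data that include oxygenation, so the information is not shown to be wholly absent. This is fair, though a partial proxy recovers only part of the loss (step 6).

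Two further readings go too far. SatO2/FiO2 is not the variable that defines the endpoint: oxygenation is one of three components and may be met on either ratio, and SatO2/FiO2 alone is not guaranteed for every patient. Prior corticosteroid exposure cannot be called a recorded but neglected covariate: section 2.7.1 names concomitant medication, not earlier steroid use.

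**Conclusion.** The point holds as an avoidable loss of efficiency, not as an error in the main test. The main estimate is unadjusted, the trial is small and unstratified, and the most directly relevant day-0 measurement is not named in either model.

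The size rests on an assumed prognostic strength and on how 0.52 is read. With g from 0.3 to 0.7 and 0.52 as the conditional hazard ratio, unadjusted power is about 76% down to 56–60%, against about 80% adjusted. With 0.52 as the unadjusted hazard ratio and g from 0.4 to 0.7, it is about 74–77% against 83–93%. The lowest figures should not be quoted as the trial's power: section 2.9.1 gives one hazard ratio without covariates, and reading B fits that at least as well. Adjustment gains power under both readings, and if oxygenation were not prognostic it would cost almost nothing (80% against 80%).

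The crowded additional model is a lesser fault. Overlap among the scores mainly wastes parameters and makes their own coefficients unstable. The type I error of about 8% comes from a simulated stand-in, not from the plan's actual model, whose marker count is unknown.

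**What to change.** Take the reported hazard ratio from a Cox model with treatment and a short, closed set of day-0 covariates: the oxygenation ratio (SatO2/FiO2 or PaO2/FiO2, under one stated rule for which is used and how patients with only the other are handled), age, and at most one severity score. Add prior corticosteroid exposure only if it is confirmed to be recorded at day 0. Keep the log-rank test, show the unadjusted hazard ratio beside the adjusted one, and replace the model that enters all the scores at once.

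State which p-value decides the primary hypothesis. If the log-rank test keeps that role, the sample size and the interim boundary stand unchanged, and the benefit is confined to the reported estimate and its interval. The power gain above reaches the formal decision only if the adjusted treatment test is named as primary, at the interim analysis as well.

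The cost is mainly wording, plus a check of which ratio each patient has and whether prior steroid use is captured. Because the trial is open-label and recruiting (section 2.13), the change should be fixed and dated before any comparison by arm is seen. The one downside is small: the adjusted hazard ratio is conditional on the covariates and will differ from the unadjusted one, which is why both are shown.
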